**Figure 1 f1:**
[figure not shown]
Overview of the study design. After screening and a 1-week run-in period, eligible participants are randomly assigned to either exercise group or control group (n = 50 per group) for 16-week intervention. During the whole trial, participants in exercise group receive combined aerobic and resistance exercise training three times a week, and control group maintain their sedentary lifestyle unchanged. All participants receive a diet administration during the intervention. In addition, participants take part in a follow-up visit every four weeks.

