### Participants and Recruitment

The study will include adults aged 35-65 years of any sex, who have been diagnosed with type 2 diabetes mellitus and are not insulin-dependent. Potential participants will be recruited at the Shanghai Jiao Tong University Affiliated Sixth People’s Hospital. The inclusion and exclusion criteria are presented in **Table 1**. The potential benefits and risks of the study will be informed to the participants before screening. Written informed consent will be obtained from all participants. Physicians will conduct a preliminary clinical evaluation to screen eligible participants, including anthropometric measurement (e.g., height, weight, body mass index, and waist, hip, and thigh circumference), blood pressure, glycated hemoglobin (HbA1c), kidney function assessment, basic information (e.g., age, sex, menopause, education, and occupation), and the questionnaire information collection (lifestyle habits, family history, and disease and medication records). If participants meet all the criteria, they will be invited to enter a run-in period, which will be followed by randomization of participants who complete the run-in period.

**Table 1 T1:** Inclusion and exclusion criteria.

Inclusion Criteria
Diagnosed with type 2 diabetes mellitus; Not more than three antidiabetic agents; The use of antidiabetic agents is stable for at least 6 weeks, and remains unchanged during the study intervention; Aged 35 to 65 years old; Abdominal obesity: waist circumference ≥ 90 cm for males and ≥ 80 cm for females; Body mass index ≤ 35 kg/m^2^; Waist to thigh ratio (WTR): male ≥ 1.7, female ≥ 1.6; Sedentary lifestyle (≤ 60 minutes of moderate-intensity activities per week).

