**Exclusion Criteria**
Glycated hemoglobin < 6.5% or ≥ 9%; Insulin usage; Presence of one or more of the following complications: severe proliferative diabetic retinopathy or worse, macroalbuminuria (urine albumin-creatinine ratio ≥ 300 mg/g), or renal dysfunction (eGFR ≤ 60 ml/min/1.73m^2^); History of cardiovascular events, including myocardial infarction, percutaneous coronary intervention, unstable angina, heart failure, and cardiac insufficiency; History of cerebrovascular diseases, including hemorrhagic and ischemic stroke; Muscle, bone, or neuromuscular injuries, and so on that will prevent exercise training; Severe osteoporosis, or suboptimal bone density test results even after treatment; Pregnancy; Not able or unwilling to undergo magnetic resonance imaging, including claustrophobia, implantable cardioverter defibrillator and pacemaker;

10. Diagnosed depression or any mental illness rendering the patients unable to understand the nature, scope and schedule of the study; 11. atients who take drugs that are unstable or affect glucose metabolism.

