### Data Collection and Follow-Up

Participants will participate in baseline, 4, 8, 12, and 16-week follow-up visits at the Department of Endocrinology and Metabolism, Shanghai Jiao Tong University Affiliated Sixth People’s Hospital. **Table 2** shows the schedule of the study process. The clinical assessments, measurements, and data collection will be conducted by independent researchers who have been trained before the study. Apart from the anthropometry and hematology examination, physicians will also perform a series of clinical assessments, including bioelectrical impedance analysis, MRI of abdomen and lower limbs, magnetic resonance spectroscopy, liver transient elastography, endothelial function ultrasound, flash glucose monitoring, heart rate variability analysis, and exercise-related tests (**Table 2**). The international physical activity questionnaire will be completed to evaluate habitual physical activity over the previous seven days, and a three-dimensional accelerometer tester (wGT3x-BT, Manufacturing Technology Inc, MTI, Florida, America) will be used to continuously monitor the basal physical activity over the following seven days on visit 1, 3, and 5. The dietary habits will be assessed through the three-day food record and food frequency questionnaire. In addition to assessment through conventional questionnaires (e.g., 100-mm visual analog scale, Patient Health Questionnaire-9, Generalized anxiety Disorder scale-7, Problem Areas in Diabetes scale, and Montreal Cognitive Assessment Scale), the brain health of the participants will be accurately evaluated by fMRI. All questionnaires will be filled by participants with the help of trained researchers during a face-to-face interview. Furthermore, blood, urine, stool, and saliva samples will be collected before and after intervention for further multi-omics analysis. Detailed methods of measurements and evaluations are described in the **Supplementary Material**.

**Table 2 T2:** Schedule of the study process.

Time point	Screening	Visit 1	Visit 2	Visit 3	Visit 4	Visit 5
	-2 weeks ~ 0 week	0week	4 weeks	8 weeks	12 weeks	16 weeks
**Eligibility screening**	✓					
**Informed consent**	✓					
**Anthropometrics** (height, weight, body mass index, and waist, hip, and thigh circumference)	✓	✓	✓	✓	✓	✓
**Bioelectrical impedance analysis** (fat mass and percentage, lean mass and percentage)		✓	✓	✓	✓	✓

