### Statistical Analysis

Both the intention-to-treat and full analysis set analyses will be performed to examine effectiveness of exercise intervention on type 2 diabetes patients with abdominal obesity and low thigh circumference. Statistical analyses will be performed using SPSS 25.0 software (SPSS, Inc, Chicago, IL). Multiple imputations will be used to process missing values in the data. Data will be expressed as mean ± standard deviation, median (interquartile range) and percentage appropriately. Kolmogorov-Smirnov test will be used to determine the normal distribution of data. All statistical tests will be two-tailed, with a 0.05 significance level.

Baseline characteristics will be compared between groups by Student’s unpaired t-test for normal distributed data, Mann-Whitney test for non-normal distributed data, and Chi-squared test for categorical data, respectively. Comparisons between baseline and different time points (4, 8, 12, and 16-week follow-ups) in each group will be performed using paired t-test for normal distributed data and Wilcoxon signed-rank test for non-normal distributed data. Changes in clinical and multi-omics data before and after the intervention will be compared between groups using analysis of covariance, with baseline variable levels as covariates. Mixed-effect models will be performed to evaluate the effect of exercise intervention on clinical indicators. Additionally, multiple linear regression will be performed for sensitivity analysis of the main clinical variables, adjusting for age, sex, duration of diabetes, and diet. The composition of the gut microbiota will be analyzed from the metagenomic sequencing data using MetaPhlAn calculating software. Differences in the abundance of microbiota species before and after the intervention will be compared using Wilcoxon test. Differences in the abundance of microbiota between groups will be compared using Mann-Whitney test. Correlation between abundance of microbiota, metabolite levels, and clinical indicators will be analyzed using Spearman correlation and Partial correlation analysis.

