In this study, we will investigate the role of the microbiota-gut-brain axis in the metabolic benefits of exercise in patients with diabetes. Apart from the related questionnaires and scales, the appetite and cognitive function of participants will be accurately assessed through resting state and task fMRI scans, which include food cue visualization- (non-food, high-calorie, and low-calorie food pictures), inspection time-, n-back-, and flanker tasks. Meanwhile, appetite hormones (including glucagon-like peptide-1, ghrelin, and peptide YY) and cytokines (including FGF21, FGF19, fatty acid-binding protein 4, lipocalin 2, and adiponectin) levels will be measured. Furthermore, metabolomics and metagenomics analysis will be performed to provide support for the actions of gut microbiota and microbial metabolites. The relationship between clinical symptoms, brain health, and multi-omics will be further analyzed to investigate the modulation of the microbiota-gut-brain axis in the benefits of exercise for diabetes.

In conclusion, this study is the first randomized clinical trial to investigate the effect of combined exercise on diabetes patients with abdominal obesity and low thigh circumference. The findings will provide a comprehensive evaluation of exercise in patients with diabetes, reveal the underlying role of the microbiota-gut-brain axis in the physiological benefits of exercise for diabetes, and provide a new approach to research the modulation of the microbiota-gut-brain axis.

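### Eligibility has no rule on recent antibiotics or probiotic changes, so recovery from a disturbed baseline can pass for microbiota change within groups and adds noise between them

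*Protocol article*

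**What the plan says.** Table 1 of the Protocol article gives the inclusion list and 11 exclusion criteria. Three rules deal with medication:

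- Antidiabetic agents, at most three: "The use of antidiabetic agents is stable for at least 6 weeks, and remains unchanged during the study intervention".
- Insulin use is excluded.
- The last exclusion covers "atients who take drugs that are unstable or affect glucose metabolism" (its first letter is lost in the text).

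None of these names antibiotics or probiotics or sets a look-back period for them. Screening (Participants and Recruitment) does collect "lifestyle habits, family history, and disease and medication records", but no eligibility or sampling rule is attached to that information.

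On timing, the legend of Figure 1 says: "After screening and a 1-week run-in period, eligible participants are randomly assigned to either exercise group or control group". Table 2 allows at most two weeks for screening and schedules metagenomics at Visit 1 and Visit 5 only. Data Collection and Follow-Up confirms that "blood, urine, stool, and saliva samples will be collected before and after intervention for further multi-omics analysis".

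Statistical Analysis plans four things for these data: a within-group test ("Differences in the abundance of microbiota species before and after the intervention will be compared using Wilcoxon test"), analysis of covariance on baseline for between-group comparison of multi-omics changes, a Mann-Whitney test of abundance between groups, and correlations of abundance with metabolites and clinical indicators. The Discussion says that the findings will "reveal the underlying role of the microbiota-gut-brain axis in the physiological benefits of exercise for diabetes".

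**The concern.** A patient who finished a course of antibiotics shortly before Visit 1 meets every criterion in Table 1 and gives the only pre-intervention stool sample on schedule. If the microbiota then recovers during the 16 weeks, the week-16 sample differs from baseline for a reason that has nothing to do with exercise. Someone who started or stopped a probiotic just before Visit 1 is in the same position.

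The plan controls diet in both arms to reduce confounding and requires stable antidiabetic medication. It therefore accepts the principle of removing variation unrelated to exercise, but does not apply it to a direct source of such variation in the stool data.

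At stake is how the metagenomic results can be read. A within-group test cannot tell recovery from an exercise effect. Correlations of abundance with clinical measures inherit the same unexplained variation. The between-group comparison loses precision. Once the Visit 1 sample has been taken, nothing before the intervention can replace it.

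**Working it through.** **The plan's own figure.** Sample Size Estimation uses a difference of 1.2 kg, SD 1.9 kg, two-sided α 0.05 and power 80%. n = 2 × (1.960 + 0.842)² × 1.9² / 1.2² = 39.3, rounded up to 40 per group; 40 / 0.80 = 50. Both figures reproduce and neither is in dispute. The plan gives no corresponding figure for metagenomics.

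**Assumed inputs (none is in the documents).** A fraction p of patients in each arm has a displaced baseline. The displacement is d = 2 SD of the change score. Undisturbed change has SD 1, and the pre/post correlation r is 0.5 to 0.8. Week-16 values are taken as recovered.

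**Between groups, analysis of covariance on baseline.**

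- Let s² be the variance of an undisturbed measurement. A change SD of 1 means 2s²(1 − r) = 1, so s² = 1 for r = 0.5 and s² = 2.5 for r = 0.8.
- Displacement adds V = p(1 − p)d² to the baseline variance. V = 0.09 × 4 = 0.36 at p = 10%, and 0.16 × 4 = 0.64 at p = 20%.
- The residual variance, relative to no exposure, is [1 − r²s²/(s² + V)] / (1 − r²).

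| p | r | Calculation | Ratio | Effective n of 50 |
|---|---|---|---|---|
| 10% | 0.5 | (1 − 0.25/1.36)/0.75 | 1.09 | 46 |
| 10% | 0.8 | (1 − 1.60/2.86)/0.36 | 1.22 | 41 |
| 20% | 0.5 | (1 − 0.25/1.64)/0.75 | 1.13 | 44 |
| 20% | 0.8 | (1 − 1.60/3.14)/0.36 | 1.36 | 37 |

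The loss is therefore 9-22% in variance at 10% exposed and 13-36% at 20%.

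**Between groups, Mann-Whitney.** The plan does not say whether this test is applied to change or to week-16 abundance. If to change, simulation with 40 per arm and an effect of 0.63 SD (1.2/1.9, borrowed only for scale) gives power of about 77% with nobody exposed, 66% at 10% and 58% at 20%. With no true effect, the test rejects 4.2-5.6% of the time across 5-30% exposed and shifts of 1-3 SD, so there is no systematic bias. If the test is applied to week-16 abundance, a patient who has recovered by then adds no disturbance.

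**Within group, before/after Wilcoxon.** In the same simulation (40 patients, no exercise effect), the test rejects about 5% of the time with nobody exposed, 14% at 10% exposed and 37% at 20%, for a 2 SD shift. Across 5-30% exposed and shifts of 1-3 SD, the range is 6-82%. This test carries the larger risk, because recovery moves a given species in one direction and more patients do not average it away.

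**The case against.** Several counter-arguments stand and limit the point.

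- **No bias between arms.** A reader might infer that recovery biases the exercise effect. Allocation is randomized, so recovery is balanced in expectation, and the simulated type I error confirms it. The chance of unequal numbers of exposed patients (0.40 for a difference of 3 or more, at 10% exposed and 50 per arm) is ordinary sampling variation, already contained in the variance inflation. It is not a second harm.
- **Smaller size than change scores suggest.** For unadjusted change the inflation would be 1 + V, that is 36% at 10% exposed and 64% at 20%. The plan states baseline adjustment for multi-omics changes, which gives less weight to a noisy baseline, so the lower figures apply.
- **Exposure can be identified.** One might conclude that a disturbed baseline would go unseen. Medication records are taken at screening, so exposed patients could be flagged and a sensitivity analysis run without changing eligibility.
- **Not every user drifts.** A patient who takes a probiotic steadily at both samples has no recovery to show. A current short antibiotic course may already fall under the exclusion of unstable drugs. Only a completed course or a recent change clearly escapes Table 1.
- **The question has other supports.** The microbiota-gut-brain question does not rest on the stool pair alone: appetite hormones, metabolomics and fMRI also bear on it. Metagenomics is one of many secondary outcomes.
- **Unseen material.** "Detailed methods of measurements and evaluations are described in the" Supplementary Material, which is not shown and may contain a stool-collection rule. It therefore cannot be said that no rule for postponing the sample exists anywhere.

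The last argument does not dispose of the point. Eligibility is where a look-back rule belongs, and Table 1 is presented as the list of criteria rather than a summary of it. The possibility of a sensitivity analysis does not restore a usable baseline for the exposed patients either.

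**Conclusion.** The point holds in a limited form. As written, Table 1 admits patients with a recently disturbed microbiota, and the schedule gives them a single pre-intervention sample. Their recovery can look like an effect in the within-group Wilcoxon test and can enter the abundance correlations. In the between-group comparison it costs precision only.

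With 10-20% exposed, a 2 SD shift and a pre/post correlation of 0.5-0.8, that cost is about 9-36% in variance under the planned analysis of covariance. All of these inputs are assumptions; with few exposed patients or small shifts the effect would be minor. The documents do not support a stronger reading in which the exercise comparison is biased or the microbiota aim is lost. The primary outcome and the sample size are untouched. This is a cheap improvement, worth making before baseline sampling because it cannot be repaired afterwards.

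**What to change.** 1. Add one exclusion to Table 1: systemic antibiotics, or starting or stopping a probiotic, within a fixed period before the Visit 1 stool sample, with one re-screen allowed once the period has passed. The sponsor should fix and justify the period. Three months is a reviewer's assumption with no source in the documents.
2. Record antibiotic courses during the 16 weeks, with dates. This concerns recording only and changes no treatment.
3. Pre-specify a sensitivity metagenomic analysis that omits samples taken soon after a course, with that interval also set and justified in advance.
4. State that claims about the effect of exercise on the microbiota rest on the between-group comparison, and that the within-group Wilcoxon results are descriptive. State also whether the Mann-Whitney test uses change or week-16 abundance.
5. If the Supplementary Material already has a stool-timing rule, refer to it from Table 1.

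The cost is an eligibility amendment, one added question in the screening medication record, a dated log and one extra analysis. The drawback is that a small share of candidates is deferred.

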#### Secondary Outcomes

Secondary outcomes include change rate of body fat mass, and changes in lean mass and percentage, anthropometric indicators (body weight, body mass index, and waist, hip, and thigh circumference), clinical biochemical indicators (HbA1c, insulin sensitivity, liver enzyme, renal function, blood lipid, blood glucose, serum insulin and C peptide), brain health (appetite, mood, and cognitive function), immunologic function, metagenomics, metabolomics, energy expenditure, cardiopulmonary fitness (maximum oxygen uptake, maximum oxygen uptake/predicted oxygen uptake), exercise-related indicators (physical activity, grip, flexibility, lower limb muscle endurance and strength, static and dynamic balance function, and muscle oxygen), fatty liver, cytokines (fibroblast growth factor [FGF] 21, FGF19, adiponectin, fatty acid-binding protein 4, and lipocalin 2), vascular endothelial function, autonomic nervous function, and glucose fluctuation.

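### Weight, BMI, waist, hip and thigh are measured twice before training, but the planned ANCOVA, on its natural reading, adjusts for Visit 1 only; adding the Screening value as a second covariate would give a modest gain in precision

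*Protocol article*

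**What the plan says.** - **Schedule.** The Anthropometrics row of Table 2 (Data Collection and Follow-Up) covers "height, weight, body mass index, and waist, hip, and thigh circumference" and is ticked at Screening (weeks -2 to 0), Visit 1 (week 0) and every later visit.
- **Use of the Screening reading.** Participants and Recruitment states: "Physicians will conduct a preliminary clinical evaluation to screen eligible participants, including anthropometric measurement". Two of the entry criteria in Table 1 rest on it: "waist circumference ≥ 90 cm for males and ≥ 80 cm for females" and "Waist to thigh ratio (WTR): male ≥ 1.7, female ≥ 1.6".
- **Gap between the readings.** The Figure 1 legend says: "After screening and a 1-week run-in period, eligible participants are randomly assigned".
- **Baseline.** Data Collection and Follow-Up says: "Participants will participate in baseline, 4, 8, 12, and 16-week follow-up visits". Baseline is thus listed as one visit.
- **Analysis.** Between-group comparison of changes is by "analysis of covariance, with baseline variable levels as covariates". Mixed-effect models are also planned, without a statement of how baseline enters them.
- **Status of the measures.** Secondary Outcomes lists "anthropometric indicators (body weight, body mass index, and waist, hip, and thigh circumference" among many others. The primary outcome is change in fat mass by bioelectrical impedance (BIA), which Table 2 first schedules at Visit 1.

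**The concern.** A single tape or scale reading is an imperfect measure of a participant's underlying value. When it is the only baseline covariate, its error passes into the residual of the ANCOVA. A second reading taken one or two weeks earlier carries further information about the same underlying value, and here it costs nothing because it is already collected to decide eligibility. If it stays out of the model, the intervals for waist, thigh, hip, weight and BMI are somewhat wider than the scheduled data allow. Waist and thigh circumference correspond directly to the features on which participants are enrolled. What is at stake is precision on secondary outcomes, not bias.

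**Working it through.** **1. The plan's own figure.** Per group, n = 2(1.960 + 0.842)² × 1.9² / 1.2² = 39.4, so 40; 40 / 0.8 = 50 per group, 100 in total. The stated sample size reproduces. It concerns BIA fat mass, which has one pre-training reading, so nothing below changes it. It implies about 80 completers.

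**2. Model.** Let T be the true value at Visit 1, with Visit 1 reading X1 = T + e1, Screening reading X0 = T + e0, and week-16 value Y = T + δ + e2. Each reading has error variance s².
- Visit 1 as the only covariate: residual variance = var(δ) + s²(1 + reliability), close to var(δ) + 2s² when reliability is high.
- Both readings as covariates: about var(δ) + 1.5s².
- Fractional reduction: about 0.5s² / (var(δ) + 2s²).

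**3. Inputs.** The article gives no error SD, change SD or correlation. Assumed error SD: 1.0-2.0 cm for waist, 0.5-1.0 cm for thigh. Assumed SD of true change: 2-3 cm for waist, 1.0-1.2 cm for thigh.

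**4. Readings of equal quality.**

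| Measure | Error SD | Change SD | Reduction |
|---|---|---|---|
| Waist | 1.0 | 3.0 | 0.5 / 11 = 4.5% |
| Waist | 2.0 | 2.0 | 2 / 12 = 16.7% |
| Thigh | 0.5 | 1.2 | 0.125 / 1.94 = 6.4% |
| Thigh | 1.0 | 1.0 | 0.5 / 3 = 16.7% |

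These are slight overestimates, because reliability is below 1 and the Screening value is truncated by the entry criteria. Simulation with the male cut-offs (waist ≥ 90 cm, ratio ≥ 1.7), which also needs assumed population means and spreads, gives about 5-15% for waist and 6-15% for thigh.

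**5. A poorer Screening reading.** Suppose its error SD is 50% larger and true values drift between the visits with SD 0.7s. Its effective error variance is then (1.5² + 0.7²)s² = 2.74s². The best combination with Visit 1 has error variance s² / (1 + 1/2.74) = 0.73s², a saving of 0.27s² instead of 0.5s². At the low end this is 0.27 / 11 = 2.4% for waist and 0.067 / 1.94 = 3.4% for thigh. Simulation with the cut-offs gives about 2-7% for waist and 3-8% for thigh.

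**6. Interval width.** Over the full range, 1 - √0.98 = 1% and 1 - √0.85 = 8%.

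**7. Cost.** One extra covariate with 80 completers costs about 1/77 = 1.3% of variance.

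**8. Why not average.** Let R be the Screening-Visit 1 correlation and ρ the Visit 1-week 16 correlation. If Screening predicts week 16 only through Visit 1, then with R = 0.95 and ρ = 0.9 the average has residual variance 1 - 0.8775² / 0.975 = 0.210, against 1 - 0.9² = 0.190 for Visit 1 alone: a ratio of 1.11. Over R of 0.95-0.98 and ρ of 0.8-0.9, averaging costs 2-11%. Two separate covariates avoid this, because the regression chooses the weights.

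**9. Near-perfect agreement.** If R = 0.99 and both readings correlate equally with week 16, the variance ratio, 1 - 2ρ²/(1 + R) over 1 - ρ², is 0.995 at ρ = 0.7 and 0.953 at ρ = 0.95. At the first of these, the 0.5% gain does not cover the 1.3% cost.

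**The case against.** **Nothing in the plan is wrong.** ANCOVA on one baseline reading is valid, unbiased and conventional. This stands: the point is an efficiency suggestion, not the correction of an error or contradiction.

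**The single-baseline reading is inferred.** The article does not say that only Visit 1 enters the model or that the Screening value is excluded. Nor can baseline mean Visit 1 for every variable: Table 2 ticks HbA1c at Screening but not at Visit 1. An unseen analysis plan may already use both readings. This stands, and a reader who infers that the Screening reading is discarded, or precision thrown away, goes beyond the text. What remains is a specific improvement to the analysis as most naturally read.

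**The measures are secondary.** The Introduction says that abdominal obesity and muscle loss will be quantified by MRI, and the tape measures sit in a long list of secondary outcomes. This stands and limits the importance of the point.

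**Screening values are selected and may be of lower quality.** Waist and the waist-to-thigh ratio are truncated by the entry criteria, Screening is described as a preliminary evaluation by physicians, and a run-in intervenes. This reduces the gain, and the lower ranges above allow for it. It does not bias the group comparison, because the Screening value precedes randomisation. It is a good reason not to compute change from Screening, where regression to the mean would enter the change score.

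**The size rests wholly on assumptions.** True. No figure is offered for weight, hip or BMI.

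**Conclusion.** The point holds as a modest, optional gain in precision on secondary outcomes. With the assumed SDs and the male entry cut-offs, residual variance falls by about 2-15% for waist and 3-15% for thigh, or 1-8% in interval width, before a cost of about 1.3%. The net gain could be close to zero if the two readings agree almost perfectly.

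A reader might infer that the primary analysis is also short of precision, or that BIA ought to be taken at Screening as well. The article does not support either: the stated sample size reproduces, one pre-training BIA reading is an acceptable design, and a second would be a new measurement and a matter of preference.

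**What to change.** In Statistical Analysis, state for weight, BMI, waist, hip and thigh circumference that:
1. Visit 1 is the baseline from which change is computed.
2. The Screening and Visit 1 values both enter the ANCOVA and the mixed-effect models, as two separate covariates and not as their plain average.

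Settle this before the database is locked. The readings are already scheduled, so no visit, measurement or participant burden is added; the cost is one sentence in the plan and one degree of freedom per model. Nothing changes for the primary outcome or the sample size, and no additional BIA reading is requested.
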